## Abstract

**Background:**

Incidence of and mortality from colorectal cancer (CRC) can be effectively reduced by screening with the fecal immunochemical test (FIT) or colonoscopy. Individual risk to develop CRC within 15 years varies from <1% to >15% among people aged 50 to 75 years. Communicating personalized CRC risk and appropriate screening recommendations could improve the risk-benefit balance of screening test allocations and optimize the use of limited colonoscopy resources. However, significant uncertainty exists regarding the feasibility and efficacy of risk-based screening.

**Objective:**

We aim to study the effect of communicating individual CRC risk and a risk-based recommendation of the FIT or colonoscopy on participants’ choice of screening test. We will also assess the feasibility of a larger clinical trial designed to evaluate the impact of personalized screening on clinical outcomes.

**Methods:**

We will perform a pilot randomized controlled trial among 880 residents aged 50 to 69 years eligible to participate in the organized screening program of the Vaud canton, Switzerland. Participants will be recruited by mail by the Vaud CRC screening program. Primary and secondary outcomes will be self-assessed through questionnaires. The risk score will be calculated using the open-source QCancer calculator that was validated in the United Kingdom. Participants will be stratified into 3 groups—low (<3%), moderate (3% to <6%), and high (≥6%) risk—according to their 15-year CRC risk and randomized within each risk stratum. The intervention group participants will receive a newly designed brochure with their personalized risk and screening recommendations. The control group will receive the usual brochure of the Vaud CRC screening program. Our primary outcome, measured using a self-administered questionnaire, is appropriate screening uptake 6 months after the intervention. Screening will be defined as appropriate if participants at high risk undertake colonoscopy and participants at low risk undertake the FIT. We will also measure the acceptability of the risk score and screening recommendations and the psychological factors influencing screening behavior. We will also assess the feasibility of a full-scale randomized controlled trial.

**Results:**

We expect that a total sample of 880 individuals will allow us to detect a difference of 10% (α=5%) between groups. The main outcome will be analyzed using a 2-tailed chi-squared test. We expect that appropriate screening uptake will be higher in the intervention group. No difference in overall screening uptake is expected.

**Conclusions:**

We will test the impact of personalized risk information and screening recommendations on participants’ choice of screening test in an organized screening program. This study should advance our understanding of the feasibility of large-scale risk-based CRC screening. Our results may provide insights into the optimization of CRC screening by offering screening options with a better risk-benefit balance and optimizing the use of resources.

**Trial Registration:**

ClinicalTrials.gov NCT05357508; https://www.clinicaltrials.gov/study/NCT05357508

**International Registered Report Identifier (IRRID):**

DERR1-10.2196/46865

## Introduction

### Background

Colorectal cancer (CRC) is the third most common cancer after breast and lung cancers [1]. In 2020, CRC affected approximately 2 million people worldwide and caused 900,000 deaths. In Switzerland, every year, 4500 people are diagnosed with CRC, of whom 1760 die from CRC [2]. However, CRC can be effectively prevented by screening that allows detection and removal of early-stage cancers and precancerous lesions [3-5]. The 2 most frequently offered screening options are colonoscopy and the fecal immunochemical test (FIT). Colonoscopy is more sensitive, especially for polyps [6,7], but it carries risks of bleeding and perforation [8,9]. It also requires an onerous bowel preparation; can be embarrassing for patients; and, as a population-level screening test, requires a large number of gastroenterologists. The FIT is less costly and noninvasive, can be performed at home without preparation, and has higher acceptance [6,10]. The impact of the FIT on CRC mortality over multiple rounds of screening is likely similar to colonoscopy [7,10], and it seems to decrease CRC incidence by approximately 33% [11].

Major risk factors for CRC are advanced adenoma, increasing age, and a small number of rare genetic syndromes [5]. Multiple other factors related to environment and lifestyle influence CRC incidence and can also contribute to one’s risk of developing CRC [12]. One of the best-performing risk calculators is the open-source tool QCancer [12], developed in the United Kingdom and validated on 2 large cohorts of 3.6 million and 2.1 million patients [13,14]. It performed well in comparison with other algorithms [14,15].

Currently, in Switzerland and many other countries, the population is divided into 2 groups: people at average risk of CRC and those at very high risk of CRC because of a personal history of advanced adenomas or CRC, a familial history of CRC, symptoms concerning for cancer, or rare genetic syndromes [5]. Individuals at very high risk are offered regular surveillance colonoscopies and are not part of organized screening programs. However, the population at average risk is not homogeneous and could be broken up into at least 3 groups: high, moderate, and low risk. In 2019, the BMJ Rapid Recommendations team [12] made a weak recommendation against screening for individuals with a CRC risk of <3% in the next 15 years using the QCancer calculator [12]. However, because zero risk does not exist, recommendations against screening are questionable. Nevertheless, the threshold of <3% risk can be used to recommend the FIT and not colonoscopy. In clinical practice, patients with a risk of >6% in the next 15 years are generally offered colonoscopy surveillance. Thus, 6% risk can be considered a threshold for the high-risk level.

These cutoffs could optimize the use of colonoscopy resources, which are limited. The majority of people are at low risk (approximately 60%; [name], PhD, email, June 21, 2020). Offering them colonoscopy results in its overuse and risk of complication for the individuals who are less likely to benefit from screening. On the contrary, reorienting individuals at low risk to the FIT would reduce the number of individuals who choose colonoscopy as a screening test and, therefore, reduce waiting time for those at high risk. Given that the ultimate aim of screening is to diminish mortality, colonoscopies should be reserved for people at high risk because differences in risk reduction between colonoscopy and the FIT become more pronounced for this population [16].

However, the impact of personalized screening on the screening test choice remains unclear. A meta-analysis has shown that personalized risk communication alone does not improve the overall uptake of screening tests [17]. Indeed, communicating personalized risk without giving clear screening recommendations may have no influence on screening behavior or even decrease it. This is in accordance with the view that providing people with threatening information only can decrease desired health behaviors if people cannot cope with the threatening information. However, the studies included in the meta-analysis did not address the choice between the FIT and colonoscopy and contain some important methodological discrepancies.

### Objectives

In summary, personalized screening may offer people better risk-benefit balance in CRC screening and optimize the use of limited colonoscopy resources. However, there is limited knowledge about how the communication of risk and screening recommendations affects CRC screening behaviors. The primary aim of this trial is to study the effect of communicating individual CRC risk score and screening recommendations on appropriate screening uptake at 6 months in individuals stratified into 3 groups: low, moderate, and high risk of developing CRC in the next 15 years. Screening will be considered appropriate if the participant undertakes the test that is adapted to their risk level. Our hypotheses are as follows:

Compared with the control group, individuals at low risk receiving the intervention will be more likely to undertake the FIT.Compared with the control group, individuals at high risk receiving the intervention will be more likely to undertake colonoscopy.Individuals at moderate risk receiving the intervention will have the same screening behavior as the individuals in the control group, that is, approximately 50% will be more likely to undertake the FIT, and approximately 50% will be more likely to undertake colonoscopy [18].

We expect no difference in overall screening uptake.

Moreover, we will calculate the participation rate and proportion of individuals eligible for our study. We will also perform subgroup analyses and explore anxiety related to the information about the participants’ risk level.

## Methods

The trial’s protocol follows the SPIRIT (Standard Protocol Items: Recommendations for Interventional Trials) guidelines and the CONSORT (Consolidated Standards of Reporting Trials) statement for randomized controlled trials, as well as the CONSORT-EHEALTH (CONSORT of Electronic and Mobile Health Applications and Online Telehealth) checklist [19,20] (Multimedia Appendix 1). The trial was registered on ClinicalTrials.gov (NCT05357508) on May 3, 2022, before the enrollment of the first participant.

### Study Design and Setting

We will perform a 2-arm randomized superiority controlled trial with participants randomized 1:1 in 2 arms: intervention and usual care. Participants, but not the investigators, will be blinded. The statistician performing the primary outcome analyses will be blinded to group assignments. The trial will be nested in the Vaud CRC screening program.

We used a *patient and public involvement in research* approach throughout by involving 5 members of the target population (residents of the canton of Vaud, Switzerland, aged between 50 and 69 years) in all aspects of the project. This collaboration allowed us to develop materials for our participants that were acceptable, easily understood, and pretested before the trial started. These 5 members will participate in the interpretation and dissemination of the results.

### Participants

We plan to send out 4300 invitations to recruit 880 eligible participants (Figure 1). Refer to Textbox 1 for the inclusion and exclusion criteria.

Our exclusion criteria allow for the exclusion of individuals at very high risk of CRC (Textbox 1), enabling us to avoid inviting to the study those who are ineligible for the Vaud screening program. Individuals at very high risk are identified using a questionnaire to screen for current symptoms of possible CRC, personal history of CRC or polyp requiring surveillance, inflammatory bowel disease, and genetic syndromes.

Participants can stop their participation at any time without providing any justification. They will be informed that screening uptake is not mandatory and that withdrawal of consent will not affect their subsequent participation in the Vaud screening program.

**Figure 1 figure1:**
[figure not shown]
Planned CONSORT (Consolidated Standards of Reporting Trials) diagram for the pilot randomized controlled trial. T1: intervention and secondary outcome data collection; T2: follow-up at 6 months (primary outcome and secondary outcome data collection).

Inclusion and exclusion criteria.
**Inclusion criteria**
Being a resident of the Vaud canton, SwitzerlandAged between 50 and 69 yearsNot having yet been invited to the Vaud colorectal cancer (CRC) screening program (this program was gradually rolled out between 2016 and 2022)
**Exclusion criteria**
Current new symptoms suggestive of CRCPersonal history of CRC, inflammatory bowel disease, or advanced adenoma or other polyps requiring colonoscopy surveillance at intervals of <10 yearsHigh-risk familial syndromes for CRC (ie, Lynch syndrome or familial polyposis)Having undergone colonoscopy within 9 years or having undertaken the fecal immunochemical test within 1.5 yearsBeing unable to participate in follow-up at 6 months

### Procedure

The study will be conducted in the following 3 phases:

T0: recruitment and baseline data collectionT1: intervention and secondary outcome data collectionT2: follow-up at 6 months (primary outcome and secondary outcome data collection)

At T0, an invitation letter, a consent form, and the baseline questionnaire (questionnaire 1) that allows us to verify the eligibility criteria and calculate the CRC risk score will be sent to the potential participants by the Vaud CRC screening program. The ID codes for the participants will be generated using the IDGenerator, a software tool that was specifically developed for epidemiological and clinical trials [21]. The risk score will be calculated for all eligible individuals who return the signed consent form; subsequently, they will be randomized to either the intervention group or the control group. All individuals who do not respond within 1 month after the first mailing will receive a reminder.

At T1, enrolled participants will receive the intervention or a usual care brochure (in accordance with their group allocation), questionnaire 2, and an information sheet that they can provide to their general practitioner and pharmacist regarding their participation in the study. The participants who do not respond to questionnaire 2 within 2 weeks will be sent a reminder. Qualitative interviews will be conducted with willing participants at this time.

Six months after the intervention, at T2, participants will be contacted again to measure their screening behavior using questionnaire 3. Their responses will be accepted up to 8 months after the intervention. In case of nonresponse within 2 weeks, they will receive a reminder.

All 3 questionnaires, information materials for the participants, and the consent form will be available in both paper and electronic formats. Participants can choose the format that is more convenient to them. All data will be entered into the REDCap (Research Electronic Data Capture; Vanderbilt University) platform [22,23].

Refer to Table 1 and Figures 1 and 2 for procedure details.

**Table 1 table1:** Schedule of enrollment, intervention, and assessments.

		Study period			
		Enrollment	Allocation	After the allocation	
		T0^a^	0	T1^b^	T2^c^
**Enrollment**					
	Informed consent	✓			
	Eligibility screening	✓			
	Calculation of the risk for CRC^d^	✓			
	Allocation		✓		
**Intervention**					
	Mailing of the intervention brochure			✓	
	Mailing of the usual care brochure			✓	
**Assessments**					
	Baseline variables: eligibility, risk factors for CRC, previous screening recommendations from a GP^e^, knowledge about screening for CRC, demographics, and contact information	✓			
	Main outcome variables: FIT^f^ uptake, colonoscopy uptake or appointment for colonoscopy				✓
	Secondary outcome variables				
	Intention for screening	✓		✓	✓
	Results of the undertaken screening test				✓
	Self-efficacy for screening tests			✓	
	Emotional reaction to the received risk score			✓	
	Perceived barriers to screening			✓	✓
	Perceived benefits from screening			✓	
	Perceived susceptibility for CRC			✓	
	Quality of the brochure and acceptability of the screening recommendations			✓	
**Qualitative** **interviews**					
	Clarity, completeness, and credibility of the information in the brochure, brochure’s usefulness for decision-making, and suggestions about brochure design			✓	✓
	Motivation for undergoing a specific screening test			✓	✓

^a^T0: recruitment and baseline data collection.

^b^T1: intervention and secondary outcome data collection.

^c^T2: follow-up at 6 months (primary outcome and secondary outcome data collection).

^d^CRC: colorectal cancer.

^e^GP: general practitioner.

^f^FIT: fecal immunochemical test.

**Figure 2 figure2:**
[figure not shown]
Detailed procedure of the study. T0: recruitment and baseline data collection; T1: intervention and secondary outcome data collection; T2: follow-up at 6 months (primary outcome and secondary outcome data collection).

### Outcome Measures

The primary outcome measure is the self-reported appropriate screening uptake 6 to 8 months after the intervention (T2), measured using a short self-administered questionnaire. As waiting times can be long for screening colonoscopies [18], participants who have fixed a colonoscopy appointment will be counted as having undergone a colonoscopy. For the secondary outcome measures, refer to Textbox 2, and for the additional measures, refer to Textbox 3.

Refer to Multimedia Appendix 2 for the English version of the questionnaires and Multimedia Appendix 3 for the French version.

Secondary outcome measures.Self-reported overall screening participation measured at T2 (follow-up at 6 months): on the basis of the participants’ responses at T2, we will calculate the proportion of those who have completed any colorectal cancer (CRC) screening test (fecal immunochemical test or colonoscopy)Participation in the study at 6 weeks after the invitation letter was sent out: we will calculate the number of fully completed electronic or paper questionnairesEligibility for the Vaud CRC screening program at 6 weeks after the invitation letter was sent out: we will calculate the proportion of those who are eligible for the Vaud screening program (eg, not up to date with screening, not in colonoscopy surveillance, and no personal CRC history)Self-reported anxiety related to the intervention and control materials measured at T1 (intervention) using 6 items inspired by the State-Trait Anxiety Inventory [24]Linkage to the Vaud CRC screening program assessed at 3 to 6 months after the primary outcome measurement: we will calculate the proportion of study participants who consent and whose screening status is obtained from the Vaud CRC screening programLinkage to the Vaud cancer registry up to 10 years after the primary outcome measurement: we will calculate the proportion of study participants who consent and whose cancer status is obtained from the Vaud cancer registry (a long time frame has been chosen in view of the delay in updating the cancer registry records and interest in cancer outcomes several years after the primary outcome measurement)

Additional measures.

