#### Quantitative Data Analysis Plan

The study data will be summarized across all participants by group and by risk level. Continuous and count variables will be summarized as mean (SD) or median (IQR) and categorical variables as number (percentage). To test randomization quality, differences on the baseline variables will be examined using a 2-tailed *t* test for continuous variables and a 2-tailed chi-squared test for categorical variables.

Self-reported appropriate screening uptake will be analyzed using a 2-tailed chi-squared test and controlled for the CRC risk level. Data analysis will be performed using R statistical software (R Foundation for Statistical Computing) [31] and Stata 16 software (StataCorp LLC) [32].

For the primary outcome, participants lost to follow-up will be considered as having refused to participate in screening. If there seems to be differential loss to follow-up between the intervention and control groups, we may perform multiple imputation based on baseline factors as an exploratory analysis. For other secondary outcomes, data will be considered missing completely at random.

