## Results

### Overview

As of September 2022, a total of 515 participants had been enrolled in the trial and sent intervention or control materials. Six months later, 98.8% (509/515) of the enrolled individuals were sent the follow-up questionnaire. Data collection was completed on July 24, 2023 (6-8 months after the intervention).

We expect that the proportion of participants who complete the screening test appropriate to their risk level will be higher in the intervention group than in the control group, except for the individuals at moderate risk. The proportion of participants at moderate risk in the intervention group is expected to be the same as that of the participants in the control group in screening test choice because both tests are suggested as equal options.

We do not expect any difference in anxiety between the intervention and control groups. A Cochrane review of interventions similar to ours has shown that there was a nonsignificant trend toward decreased anxiety with risk information (standard mean difference in anxiety 0.13, 95% CI −0.29 to 0.03) [17].

Our intervention does not aim to enhance overall screening uptake; therefore, we do not expect any difference between the groups.

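### Overall screening participation is worded with different counting and missing-data rules from the primary outcome, so the planned shift from colonoscopy to FIT can bias it toward the intervention

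*Protocol article*

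**What the plan says.** The Outcome Measures section states, in the paragraph on the primary outcome, that "participants who have fixed a colonoscopy appointment will be counted as having undergone a colonoscopy", and gives long colonoscopy waiting times as the reason. It then refers the reader to Textbox 2 for the secondary outcomes. There, overall participation is derived "on the basis of the participants’ responses at T2", and "we will calculate the proportion of those who have completed any colorectal cancer (CRC) screening test", with FIT and colonoscopy named as the tests. Appointments are not mentioned.

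Table 1 places the appointment item under the primary only: "Main outcome variables: FIT^f^ uptake, colonoscopy uptake or appointment for colonoscopy".

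The Quantitative Data Analysis Plan sets two missing-data rules: "For the primary outcome, participants lost to follow-up will be considered as having refused to participate in screening", and "For other secondary outcomes, data will be considered missing completely at random".

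The Results overview says: "Our intervention does not aim to enhance overall screening uptake; therefore, we do not expect any difference between the groups". The Objectives state the same expectation, and Table 3 puts overall uptake at 70% in both arms.

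**The concern.** Two outcomes read from the same questionnaire should classify the same person in the same way. Taken literally, someone with a colonoscopy booked at follow-up is screened for the primary and unscreened for overall uptake. A non-responder is unscreened for the primary and missing for overall uptake.

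The first difference is not neutral between arms. The intervention is meant to move low-risk people, about 60% of the expected sample, from colonoscopy to FIT. By the protocol's own reasoning, colonoscopy is the test that may still be pending at follow-up. A completed-only count therefore penalises the test that controls are expected to choose more often.

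At stake is the comparison behind the expectation of no difference in overall uptake. A bias toward the intervention could mask a real fall in participation among low-risk people, which the low-risk brochure is worded to prevent. It would also make the two outcomes disagree where they should coincide. In the moderate stratum Table 3 counts either test as appropriate (control 41 + 42 = 83 of 118), so appropriate screening and overall uptake are the same event there.

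**Working it through.** **Inputs (Table 3, 392 per arm; low / moderate / high risk).**
- Control colonoscopy: 82 + 41 + 14 = 137. Control FIT: 82 + 42 + 14 = 138.
- Intervention colonoscopy: 48 + 41 + 20 = 109. Intervention FIT: 117 + 42 + 10 = 169.
- f, the share of colonoscopies booked but not done at follow-up, is not in the documents. It is assumed equal across arms and strata and is varied below.

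**The plan's own figures.** Overall uptake with every chosen test counted is (137 + 138)/392 = 275/392 = 70.2% in control and (109 + 169)/392 = 278/392 = 70.9% in the intervention arm, matching the stated 70% up to rounding. The difference is 3/392 = 0.8 points: two people come from the high-risk row (30 against 28) and one from rounding in the low-risk row, where 48 + 117 + 71 = 236 rather than 235. This 0.8 points is in Table 3 already and does not come from the counting rule.

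**Completed-only counting.** Uptake in an arm = [FIT + (1 − f) × colonoscopy]/392. The part of the arm difference due to the rule is f × (137 − 109)/392 = f × 28/392 = 7.1 points × f.

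| f (assumed) | Control | Intervention | Difference (points) | Due to the rule (points) |
|---|---|---|---|---|
| 0% | 70.2% | 70.9% | 0.8 | 0 |
| 20% | 63.2% | 65.4% | 2.2 | 1.4 |
| 30% | 59.7% | 62.6% | 2.9 | 2.1 |
| 50% | 52.7% | 57.0% | 4.3 | 3.6 |
| 100% (ceiling) | 35.2% | 43.1% | 7.9 | 7.1 |

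**By stratum.**
- Low risk: f × (82 − 48)/235 = 14.5 points × f, toward the intervention.
- Moderate risk: colonoscopy counts are equal (41 and 41), so zero.
- High risk: f × (14 − 20)/39 = −15.4 points × f, against the intervention.

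The Discussion expects a possibly larger low-risk share. With an assumed 80/15/5 mix and Table 3's percentages, the overall multiplier becomes 0.80 × 14.5 − 0.05 × 15 = about 10.9 points × f.

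**Chance of a false signal.** With 392 per arm, the chance that the artefact alone reaches two-sided p < 0.05 in favour of the intervention is about 6% at f = 20%, 9% at 30% and 17% at 50%.

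**Missing-data rules.** Take 70% uptake among responders and the planned 10% attrition in each arm. Counting non-responders as not screened gives 0.90 × 70% = 63% in both arms; leaving them out gives 70% in both. The level differs by 7 points, the arm difference by none. If loss were 10% in one arm and 5% in the other (assumed), the first rule gives 63% against 66.5% and the second gives 70% in both, so the rules disagree by 3.5 points.

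**The case against.** The strongest reply is that the appointment sentence is a general classification rule. It is not expressly limited to the primary, its reason applies to any count of colonoscopies, and it stands just before the pointer to Textbox 2. Someone already counted as having had a colonoscopy could then fall within Textbox 2's definition. Table 1 lists no separate overall-uptake variable, and Table 3 derives both outcomes from one set of counts with no completed-only category. This stands as a possible reading. It does not settle the matter, because Textbox 2 asks for completed tests and Table 1 ties appointments to the main outcome.

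A reader might infer that the shift to FIT must by itself produce an apparent uptake gain. The documents do not support that. They say only that waits can be long and give no pending share. Accepting responses up to 8 months leaves more time for booked procedures to be done. The high-risk stratum pulls the other way, and the artefact would rarely be significant alone.

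A reader might also infer that non-responders are dropped from overall uptake and that this adds to the gain. No sentence says they are dropped; it is inferred from the use of follow-up responses and the missing-completely-at-random sentence. Even if they are dropped, equal attrition moves both arms together.

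It is also fair that this is a secondary outcome in a pilot, with no stated test, margin or decision rule, and that detailed coding may sit in an analysis plan not shown. But the article itself states the rules, and as stated they do not match.

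**Conclusion.** The inconsistency is real and worth correcting; a bias is possible, not demonstrated. As worded, overall participation and the primary outcome differ in how they treat booked colonoscopies and non-response.

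If completed-only counting is applied, the comparison is biased toward the intervention by 7.1 points × f: 1.4 to 3.6 points for f between 20% and 50%, and nothing if f is zero. This rests on Table 3's hypothesised choices and on an assumed f common to both arms. It does not hold in every stratum: it doubles to 14.5 points × f in low risk and reverses to −15.4 points × f in high risk. If the sponsor meant the appointment rule for both outcomes, this bias disappears and only the wording needs correcting.

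The missing-data mismatch stands separately. It makes the two outcomes' levels non-comparable and affects the arm comparison only under differential loss. Neither issue touches the primary analysis or its sample size.

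**What to change.** - In Textbox 2, define overall uptake as FIT done, or colonoscopy done or booked, and make Table 1 agree.
- Handle follow-up non-responders for overall uptake exactly as in the primary.
- Limit the missing-completely-at-random assumption to outcomes other than screening uptake.
- Report completed-only tests as a sensitivity analysis for both outcomes, showing booked and completed colonoscopies separately by arm, so that f is visible.

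The cost is a few sentences and a little extra analysis. Table 1 already schedules both uptake and appointment at the 6-month follow-up; the separate display assumes that the questionnaire (an appendix not shown) distinguishes them. Counting non-responders as not screened lowers the reported uptake level, for example from 70% to 63% at 10% loss. The article says data collection is complete, so the definition should be fixed before the outcome is analysed or, failing that, stated openly in the report.
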